### Sample size {14}

A recent meta-analysis of the effects of parenting programs [15] on child maltreatment prevention showed moderate effect sizes (total random effect size of *d*=0.3 in 37 studies), which vary by intervention program, target population, and outcome measure. Moderator analysis showed that programs applied in selected or indicated samples had stronger effects than those in universal samples. Effect sizes for the APQ subscales reported in the literature vary between small to moderate effect sizes and are reported for different samples and therapeutic interventions: In a study including a risk sample of formerly incarcerated mothers effect sizes for the subscales vary between *d*=0.09 and *d*=0.32 [45], in another study including parents at risk for physical abuse between *d*=0.32 and *d*=0.65 [46]. Other studies assessing the APQ included parents of children with behavioral problems [58] or attention deficit hyperactivity disorder [59] and report effect sizes for the subscales between *d*=0.03 and *d*=0.62 with the majority of the subscales showing effect sizes between *d*=0.41 and *d*=0.49. Based on these results, we expect in this selected sample and for the APQ, an effect size of 0.35 to 0.45. A sample size calculation based on a two-sided *t*-test (significance level *α*=5) with a power of 80% for a superiority test with an alternative of an expected effect size of *d*=0.4 (difference in change in the primary outcome measure APQ from T0 to T2 between MB-PC and SCC+ arms) leads to a required sample size of 100 patients per group (using G*Power 3.1.9.2); for a true effect size of *d*=0.45 or *d*=0.35, this sample size would lead to 89% or 69% power. Note that the actual primary analysis will be multivariate for the five APQ-subscales and adjusted for covariates (see below), which is expected to provide even higher power. We expect low intra-cluster correlation (ICC; within intervention groups as used in clustered randomization or by therapists delivering the intervention), as in MB-PC 7 of 12 h are individual sessions and only 5 h are in a group-setting and the control intervention workshop does not contain any specific group exercises. However, to account for a potential small ICC of 0.02 to 0.05 [60] together with the expected cluster size (size of therapy group) of N=5, this yields a variance inflation factor (VIF) of 1.08 to 1.2. We decided to use a VIF of 1.1, thus increasing sample size by 10%. Assuming additionally up to 15% of randomized patients without any data post-baseline leads to a required sample size of 260 randomized patients.

Regarding the two sub-studies, based on power estimates and sample size calculation for mediation analyses [61], we may expect sufficient power (>80%) with a sample size of 177, respectively 120 patients, if there are small to medium direct and mediator effect sizes among the different predictor, outcome, and mediator variables.

### Recruitment {15}

Following the design of a pragmatic RCT in “real-world” clinical settings, all mothers and fathers of 1.5–15-year-old children with regular contact to their children, consecutively admitted to psychiatric hospital care at the Department of General Psychiatry at the University Hospital Heidelberg and the Psychiatric University Hospital Charité at St. Hedwig Hospital in Berlin, will be asked to participate in the trial. Furthermore, patients from the psychiatric institutional outpatient departments (PIA) offering high-frequent multi-professional treatment for patients with severe mental disorders are included. The populations in the two psychiatric hospitals differ in socioeconomic status (SES), with the University Hospital Heidelberg being located in a medium-sized high-SES town and the Psychiatric University Hospital Charité at St. Hedwig Hospital in a metropolitan region with a rather low SES, socially troubled areas and high rates of immigrants. The sample will hence be representative for urban German psychiatric care, making the outcomes essential for future clinical decisions in broad segments of the population. At each of these two study sites 130 patients will be recruited to take part in the RCT. Patients that take part in the RCT will be asked to participate in the sub-studies. The study on social cognition will recruit 104 patients at each site, the study on biobehavioral synchrony will recruit 73 patients with children aged 3–15 at each site. The sub-studies will include 30 healthy controls at each study site, too. The trial flow is shown in Fig. 1.

## Assignment of interventions: allocation

### Sequence generation {16a}

Patients are randomised in clusters of 4–8 patients who will have all their group sessions together. The allocation sequence of intervention groups to the two arms will be based on computer-generated random numbers. Randomization will be first stratified by center (Heidelberg and Berlin, each group consists only of patients from one centre) and within center balanced for treatment setting (in- or day-patient vs. outpatient, each group can consist of patients of all of these settings), using a dynamic minimization algorithm [62], which is adapted for cluster-randomization [63]. In the original version of this algorithm, the next unit to be randomised is assigned in a deterministic way to one arm (based on current imbalance); however, to make the randomization less predictable and ensure concealment of allocation, this is amended by a biased-coin design [64].

### Concealment mechanism {16b}

Concealed randomization after definite inclusion of a complete group of 4–8 patients will be performed by IMIS Kiel, via e-mail. The IMIS Kiel is not involved in recruitment, assessments or therapy of the patients.

### Implementation {16c}

The allocation sequence will be generated by the IMIS Kiel. The IMIS Kiel will also assign participant groups to interventions. At each study center study personnel not involved in recruitment, data assessment or therapy of the patients will inform the patients about the dates of the group sessions (either for MB-PC and for SCC+).

## Assignment of interventions: Blinding

### Who will be blinded {17a}

Patients and therapists cannot be blinded regarding treatment allocation in a psychological intervention. The primary outcome measure will be obtained from self-report (thus cannot be assessed in a blinded way). Since patients will be ensured that their ratings will not become known to therapists, we expect no relevantly biased assessment of results to occur. All personnel involved in recruitment and data assessment including experimental sessions will be blinded regarding treatment allocation of the patients.

### Procedure for unblinding if needed {17b}

Not applicable as patients and therapists cannot be blinded regarding treatment allocation (see the “Who will be blinded {17a}” section).

## Data collection and management

### Plans for assessment and collection of outcomes {18a}

In addition to the primary and secondary outcome measures (see above), the following data will be assessed: Sociodemographics (i.e., gender, age of parent and child, socioeconomic status, etc.); interviews administered by experienced diagnosticians (master’s degree in psychology or equivalent) will be used to assess Axis I disorders (Diagnostic Short Interview for Mental Disorders; Mini DIPS) [65], Borderline Personality Disorders (International Personality Disorder Examination, IPDE) [66] and levels of personality functioning (brief form of semi-structured Interview for Personality Functioning; StiP) [67]. Diagnosticians will also evaluate the global functioning according to the Global Assessment of Functioning, GAF [68]. Furthermore, self-report questionnaires will be used to assess symptom severity (Brief-Symptom-Inventory, BSI-53) [69], depressiveness (BDI) [70], early life maltreatment (Childhood Experience of Care and Abuse Questionnaire, CECA-Q [71]; Childhood Trauma Questionnaire, CTQ) [72], and attachment (Relationship Structures Questionnaire, ECR-RS, [73]. The mini-q [74] will be used to assess cognitive capacity. All questionnaires and semi-structured interviews are widely used in psychiatric research and have good reliability and validity.

Study a comprises four behavioral tasks and three fMRI tasks on five different aspects of social cognition: empathy, compassion, affect recognition, and affective and cognitive ToM. We use well-established tasks slightly changed in design to fit the purpose of the present study (i.e., showing pictures of children instead of adults). Parents will be asked to perform four computer-based tasks: first, a photo-task to study empathy and compassion, in which subjects view photos of affective child scenarios; second, a morphing task to study affect recognition [75]; third, an empathy and compassion task (adopted from [76]) in which subjects view affective child scenarios; and finally, a video task (adopted from [77]) assessing compassion and cognitive ToM, in which subjects will be presented with short videos of adults describing situations of emotionally neutral or negative content. In the MR scanner, subjects will be asked to perform three tasks: first, a ToM task, in which subjects view drawings of children in different affective situations; second, a pain empathy task (adopted from [78]), in which photos of children in physical painful or non-painful situations will be shown; and, lastly, a face task (adopted from [79]) in which specific statements followed by child faces in different emotional expressions will be shown (happy, sad, afraid, angry) and subjects will have to judge whether the depicted statement matches the picture of the child.

Study b uses a standardized experimental design to assess biobehavioral dyadic synchrony:

Biobehavioral synchrony will be measured within a parent-child interaction paradigm at T0 and T2. This paradigm includes a positive dyadic interaction (i.e., planning a positive joint activity) as well as a stressful dyadic interaction (i.e., solving unsolvable puzzles under time pressure) under controlled laboratory conditions. On the behavioral level, synchrony between parent and child will be measured using the Coding Interactional Behavior-System (CIB; Feldman, 1998). On the biological level, parent-child synchrony of both autonomous nervous system (ANS) activity (i.e., heart rate and heart rate variability) and hormonal release (i.e., cortisol and oxytocin) will be assessed. Study b further administers behavioral tasks on social cognition (empathy, compassion, affect recognition, and ToM) adapted to the age of the child. Children from 3 to 6 years of age will first be presented selected tasks from the Strange Stories task battery [80] and the Extended Theory-of-Mind Scale [81] and the complete Test of Emotion Comprehension [82] to assess ToM. Second, the “Affect Recognition” scale from the NePsy (“A Developmental NEuroPSYchological Assessment” [83]) will be administered. To assess empathy in preschool children, parents will be asked to complete the Empathy Questionnaire (EmQue [84]). Children from 7 to 15 years of age will first perform an almost identical version of the photo-task described above (parental assessment) to study empathy and compassion. Second, to assess ToM-selected tasks from the Strange Stories task battery [80] and a range of advanced ToM tasks will be administered [85]. Third, an almost identical version of the morphing task as described above (parental assessment) to study affect recognition [75] with age adapted instructions will be presented.

### Plans to promote participant retention and complete follow-up {18b}

All participants will be asked to participate in the post-intervention (T1) and follow-up assessments (at T2), even if they drop out of treatment, in order to minimize the number of those lost to follow-up. To keep missing data low, we will reimburse patients for the assessment of primary and secondary outcomes and will offer to visit patients at home at T2.

### Data management {19}

Data management is administered via a central data bank (Redcap). Self-report questionnaires are completed online via Lime-Survey, also interviews and measurement reports have been digitalized and made available online, all information for evaluations was compiled, and evaluation routines for all questionnaires were written prior to data collection. All details of data management procedures can be found in a separate study plan available to all study personnel.

### Confidentiality {27}

All data are subject to medical confidentiality and will be handled in accordance with the European Union General Data Protection Regulation (DSGVO) and with the German legal regulations regarding data protection and security (Landesdatenschutzgesetz Baden-Wuerttemberg, Bundesdatenschutzgesetz). All data will be pseudonymised and transferred to a server of the company netcup (Nuremberg, Germany), the transfer will be encrypted. Access to the data will be strictly limited to authorized persons and will be password-protected. Data will be stored for 10 years.

### Plans for collection, laboratory evaluation, and storage of biological specimens for genetic or molecular analysis in this trial/future use {33}

Not applicable as no biological specimens were collected as part of this trial.

## Statistical methods

### Statistical methods for primary and secondary outcomes {20a}

Superiority of the MB-PC intervention regarding APQ scores at T2 compared to SCC+ will be tested at a two-sided significance level of 5%. In the primary analysis, we will use data of both the T1 and T2 assessments (to estimate treatment contrast at T2) in a linear mixed-effects model, with all five APQ subscores as dependent variables in a multivariate model to test for global differences between arms, followed by appropriate post hoc tests for the subscores individually [86]. The analysis will include the covariates used for randomization: center, and treatment setting, and as additional covariates the gender of parent and child, the age of child, the baseline value (T0) of the primary outcome (all 5 APQ subscores), and the primary ICD-11 diagnosis at T0. Analyses of secondary outcomes will be conducted analogously. Safety analyses: Frequencies of AEs and SAEs in all randomized participants will be tabulated, separately for intervention and control group and by presumed relation to intervention and severity.

Statistical analysis will use the software R (http://www.R-project.org). All details will be specified in the statistical analysis plan prior to any data analysis.

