## Trial design {8}

Cluster-randomized, open-label (partially observer-blind), active-control, parallel group superiority clinical trial, with MB-PC groups of 4–8 patients as clusters and 1:1 allocation ratio for clusters.

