### Methods for additional analyses (e.g., subgroup analyses) {20b}

We will perform subgroup analyses in patients with and without ELM for primary and secondary outcomes.

To test the hypothesis that MB-PC-related behavioral and neural changes in social cognition as well as changes in biobehavioral synchrony will mediate the effects of the MB-PC intervention, we will test the indirect effect of MB-PC (proposed predictor) on outcome scores via parental social cognition and via biobehavioral synchrony (proposed mediators), respectively in a multiple mediator analysis using ordinary least squares regressions with bootstrapping.

To test the hypothesis that ELM will moderate the effects of MB-PC on social cognition and biobehavioral synchrony, we will calculate generalized linear (mixed) models with history of ELM (yes/no) and intervention group (MB-PC versus SCC+) as between-subject factors. A positive interaction between the factors intervention and ELM will indicate that MB-PC exerts particularly high effects in parents affected by ELM.

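### Therapy groups are randomized and the sample size allows for them, but the analysis text names no group effect in the primary model and states mediation as OLS with bootstrapping.

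*Protocol article*

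**What the plan says.** Trial design {8} describes a cluster-randomized trial "with MB-PC groups of 4–8 patients as clusters and 1:1 allocation ratio for clusters". Sequence generation {16a} repeats it: "Patients are randomised in clusters of 4–8 patients who will have all their group sessions together". Participant timeline {13} shows that groups are formed first and then allocated together to either arm, so both arms are clustered.

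Sample size {14} expects correlation within intervention groups or by therapist. It takes an ICC of 0.02–0.05 and a group size of 5 and states that "this yields a variance inflation factor (VIF) of 1.08 to 1.2". It settles on 1.1 and, after a 15% allowance for patients without post-baseline data, reaches 260 randomized.

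Statistical methods {20a} says that superiority on the Alabama Parenting Questionnaire (APQ) at T2 "will be tested at a two-sided significance level of 5"%. The model is a multivariate linear mixed-effects model of the five APQ subscores, using T1 and T2 data. The covariate sentence begins "The analysis will include the covariates used for randomization: center, and treatment setting, and as additional covariates" and lists the sex of parent and child, child age, the baseline subscores and the primary diagnosis. No random effect of any kind is named. Secondary outcomes are handled in the same way, and details are left to the SAP, which is not at hand.

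Methods for additional analyses {20b} specifies mediation as a "multiple mediator analysis using ordinary least squares regressions with bootstrapping". The moderation analysis by early life maltreatment (ELM) is a generalized linear, possibly mixed, model with maltreatment history and arm as factors.

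**The concern.** Arm is constant within a therapy group, so every between-arm contrast is a contrast between groups. If patients in a group resemble each other, a model that treats them as independent understates the standard error of that contrast, and its tests reject too often. The mixed model does not settle the matter by its name: repeated times and five subscores already call for patient-level random effects or an equivalent covariance structure, and these do not absorb correlation between patients in the same group.

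The sample size section pays for this correlation. The analysis text then gives a fairly detailed covariate list, including the factors used to balance randomization, but not the randomized unit. The mediation sentence goes further, because it names a method. OLS has no group term, and no resampling unit is given; the usual bootstrap of patients would treat them as independent. The path from arm to mediator is a between-group contrast and takes the full effect of clustering.

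At stake are the level of the primary test, the intervals for secondary and moderation effects, and the intervals for the indirect effects, which address one of the stated hypotheses.

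**Working it through.** **Inputs (Sample size {14} unless noted).** Two-sided 5% test; "with a power of 80% for a superiority test"; "alternative of an expected effect size of *d*=0.4"; 100 patients per arm before inflation; ICC 0.02–0.05; group size m = 5 (range 4–8 from Trial design {8}); variance inflation factor (VIF) 1.1; 15% without post-baseline data; 260 randomized.

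**1. The plan's own figures.**
- The exact two-sample t calculation at d = 0.4 gives 100 per arm (power 80.4%). With 100 per arm, power is 88.6% at d = 0.45 and 69.2% at d = 0.35, against 89% and 69% stated.
- VIF = 1 + (m − 1) × ICC. At m = 5: 1 + 4 × 0.02 = 1.08 and 1 + 4 × 0.05 = 1.20, as stated.
- 200 × 1.1 = 220, and 220 / 0.85 = 258.8, so 259 against 260 stated.

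The sample size reproduces and is not at fault.

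**2. Standard error if groups are ignored.** The naive standard error is 1/√VIF of the true one.
- ICC 0.02: 1 − 1/√1.08 = 3.8% too small.
- ICC 0.05: 1 − 1/√1.20 = 8.7% too small.

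**3. True level of one nominal 5% test.** α = 2 × [1 − Φ(1.96/√VIF)].

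| m | ICC 0.02 | ICC 0.05 |
|---|---|---|
| 4 | 5.7% | 6.8% |
| 5 | 5.9% | 7.4% |
| 8 | 6.6% | 9.2% |

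At m = 5 and the VIF of 1.1 used for the sample size, α = 6.2%. A simulation with 52 groups of 5 (260/5), 15% dropout and 20,000 runs gave 5.5% and 7.2% at ICC 0.02 and 0.05, and 5.1% at ICC 0.

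**4. Five-subscore global test.** Approximation: P(χ² with 5 df > 11.07/VIF) = 6.8% and 10.0%. The same simulation with a Hotelling test gave 6.7% and 9.1%, and 5.0% at ICC 0. It assumed the same ICC in every subscore and a 0.3 correlation between subscores at both group and patient level. The documents give neither. The Hotelling test stands in for the planned mixed-model test.

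**5. After the fix.** With 260 × 0.85 = 221 analysed, about 110 per arm, the effective number per arm is 110/VIF. Power at d = 0.4 is Φ(0.4 × √(n/2) − 1.96).

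| ICC | VIF | Effective n per arm | Power | Randomized patients needed |
|---|---|---|---|---|
| 0.02 | 1.08 | 101.9 | 81% | 216/0.85 → 255 |
| 0.025 | 1.10 | 100.0 | 81% | 220/0.85 → 259 |
| 0.05 | 1.20 | 91.7 | 77% | 240/0.85 → 283 |

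**6. Mediation.** The documents give no ICC for the mediators and no bootstrap unit, so only the direction can be stated: at a positive ICC, intervals from resampling patients are too narrow.

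**The case against.** The strongest reply is that this reads silence as error. The covariate sentence lists adjustment covariates, not the whole model. It also omits arm, time and any patient-level random effect, all of which the model must handle in some way, so absence from the list does not prove absence from the model. A mixed model can carry a group effect, the design and sample size sections show awareness of clustering, and the random-effects structure is a normal SAP detail. This stands. A reader might infer that the primary 5% error rate is not kept; the documents do not support that, because they neither include nor exclude the group.

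It also stands that the 5% level is stated for the APQ comparison only. Mediation is a mechanism analysis in the sub-studies with no stated level, so its method cannot breach the primary error rate. OLS estimates combined with resampling of whole groups would even be compatible with the sentence as written.

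The size should not be pushed upward. Global-test levels of 8.7–13.8% can be produced, but they need every group at the maximum of 8, where the protocol expects 5, together with the same unsupported assumptions on correlation and ICC. The protocol also gives reasons to expect a low ICC: 7 of the 12 hours are individual sessions, and the control workshop has no specific group exercises. At ICC 0 nothing is inflated.

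The reply does not dispose of the point. Whether the randomized unit enters the model decides whether the primary test is valid, and the sample size has already been raised for it. The mediation sentence names a method that, as written, makes no provision for the groups.

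**Conclusion.** The concern holds in limited form. The randomized therapy group appears in the design and the sample size but nowhere in the analysis text. For the primary, secondary and moderation models this is an unstated term that needs to be fixed in writing, not a demonstrated error. For mediation it is a stated method without cluster handling.

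If the groups were ignored at the protocol's ICC of 0.02–0.05 and groups of 5, a single test would run at about 6–7%, and the global test at about 7–9% under equal ICCs and a 0.3 correlation between subscores. Standard errors would be about 4–9% too small. These figures depend on the group being left out and on the ICC being above zero. For mediation the consequence is intervals that are too narrow.

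**What to change.** - **Primary and secondary models:** name the randomized therapy group as a random effect (for each subscore in the multivariate model), with Kenward–Roger or Satterthwaite degrees of freedom reflecting about 52 groups.
- **ELM moderation models:** include the same group effect.
- **Mediation:** use a multilevel mediation model, or keep the regressions and resample whole therapy groups within arm and centre. State the resampling unit.

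If the SAP already does this, one sentence in {20a} and one in {20b} are enough.

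The cost is wording and slightly wider intervals. No further patients are needed for an ICC up to about 0.025. At 0.05 the 1.1 inflation falls short of the 1.2 required, and power at d = 0.4 is about 77% rather than 80%, which should be acknowledged. The sub-study paragraph of Sample size {14} states no cluster allowance, so wider mediation intervals are not shown to be covered there.

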## Introduction

### Background and rationale {6a}

Poor parenting is a crucial mediator of the intergenerational continuity of child maltreatment. Parents’ mental illness (MI) and parental history of early life maltreatment (ELM) are known to be the most significant risk factors in this vicious cycle of abuse: MI and a history of ELM are both associated with child abuse potential [1]. Ten years ago a guidance of the World Psychiatric Association (WPA) has been dedicated to the protection and promotion of mental health in children of persons with severe mental disorders indicating that not the diagnosis but severity and chronicity of psychopathology confer an increased risk for child maltreatment [2]. Furthermore, it has been shown that ELM alone does not significantly impact on parenting behavior but that mothers with a history of MI and severe ELM show a particularly high risk of low maternal sensitivity in interaction with their children [3, 4]. About 3.8 million minors in Germany live in families with an MI parent [5]. In a nationwide survey of mental health professionals at psychiatric hospitals in Germany, 38.3% of the surveyed evaluated their patients as being impaired in parenting, at least sometimes, and 52.3% of the surveyed estimated the mental health of their patients’ children to be jeopardized [6]. Furthermore, MI parents often consider their children as having more psychological/behavioral problems and express a higher need for help in parenting than a healthy control group [5]. It is important to note that investigations of parenting report statistical associations in large samples. Many parents with severe mental illnesses show excellent caregiving that means a parental MI or experience of ELM do not necessarily lead to poor parenting and it is not inevitable that there is a negative impact on the children’s development. Nevertheless, children living in a family with an MI parent run a higher risk of being affected by various modes of ELM [7] and of developing psychopathology [8]. Although studies on parent-child-interaction and maltreatment of minors have been widely restricted to mothers, it has also been shown that ELM in fathers predicts harsh parenting [9] and parental neglect [10]. Additionally, MI such as depression in fathers is associated with, e.g., more withdrawn parental behavior [11] and increased risk of child maltreatment [12]. Hence, prevention programs for families with an MI parent, which pay particular attention to experiences of ELM in the parent, are urgently needed.

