
The Guidelines of the World Psychiatric Association (WPA) outline impaired responsiveness to the child’s needs, emotional unavailability, irritability, and disturbed behaviors as common pathways through which MI in parents, irrespective of the specific diagnosis, impact on their child’s well-being [2]. These pathways interact strongly with poor mentalizing, which has been shown to be a significant mediator of poor parenting and to be particularly impaired by ELM [13]. Thus, mentalization-based (MB) interventions foster social cognition in parents and provide an important and at the same time trainable basis on which to improve parents’ capacity to understand the meaning of their child’s behavior, resulting in more adaptive interactions and prevention of maltreatment [14].

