**Fig. 1 Fig1:**
[figure not shown]
Trial flow

**Table 1 Tab1:** Overview of the assessments at the different time points

Assessment	Study enrollment	Timepoint study period		
		T0 (pre-intervention)	T1 (post-intervention)	T2 (14 weeks after end of intervention)
Eligibility screen	x			
Informed consent patient and assent child	x			
Primary outcome measure Alabama Parenting Questionnaire (APQ)		x	x	x
Secondary outcome measures (self-report questionnaires on parental stress, parental abuse potential, parental mentalizing capacity, child psychopathology, and child well-being)		x		x
Other measures (diagnostic interviews and self-report questionnaires)		x		
Social cognition paradigms patients (behavioral and fMRI)		x	x	
Social cognition paradigms children 3years and older		x		x
Biobehavioral synchrony paradigm		x		x

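### The primary model adjusts for diagnosis but not for T0 symptom severity, so some precision that the already collected BSI-53 could supply is probably forgone

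*Protocol article*

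**What the plan says.** Section {20a} (statistical methods for primary and secondary outcomes) names the covariates of the confirmatory model: "The analysis will include the covariates used for randomization: center, and treatment setting, and as additional covariates the gender of parent and child", then the age of the child, and finally "the baseline value (T0) of the primary outcome (all 5 APQ subscores), and the primary ICD-11 diagnosis at T0". Secondary outcomes are to be analysed in the same way. No severity score is in the list.

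The background section {6a} cites professional guidance that "not the diagnosis but severity and chronicity of psychopathology confer an increased risk for child maltreatment". The next paragraph describes pathways from parental illness to the child's well-being that act "irrespective of the specific diagnosis".

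Section {18a} states that "self-report questionnaires will be used to assess symptom severity (Brief-Symptom-Inventory, BSI-53"), alongside a depression inventory and a clinician rating of global functioning. Table 1 places the row "Other measures (diagnostic interviews and self-report questionnaires") at T0 only, the same time point as the baseline APQ.

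The sample size section {14} says that covariate adjustment is expected to raise power, but takes no credit for it in the calculation.

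**The concern.** The model holds the patient characteristic that the cited guidance plays down (diagnosis) and omits the one that it stresses (severity), although severity is measured at T0. Because {20a} names the covariates outright, this is a stated choice and not a detail left open.

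Two things could be lost:

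- **Precision.** If T0 severity predicts T2 APQ beyond the listed covariates, leaving it out keeps residual variance in the model that could be removed at almost no cost. That works against the purpose {14} gives for adjustment.
- **Some protection against selective loss.** {14} allows for up to 15% of patients with no post-baseline data. For them only baseline covariates can make the missing-at-random assumption plausible. The arms differ in burden: 12 hours over 5 weeks against one 90-minute workshop. If severe patients went missing more often from one arm only, the contrast could shift.

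**Working it through.** **1. The plan's own figures.** Inputs from {14} and {20a}: the comparison "will be tested at a two-sided significance level of 5" per cent, "with a power of 80% for a superiority test with an alternative of an expected effect size of" d = 0.4, a variance inflation factor of 1.1, and 15% loss.

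- Two-sample t-test, d = 0.4, 80% power: 99.08 per arm, so 100. Stated: 100.
- Power with 100 per arm: 88.6% at d = 0.45 and 69.2% at d = 0.35. Stated: 89% and 69%.
- Total: 200 × 1.1 = 220; 220 / 0.85 = 258.8, so 259. Stated: 260.

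All reproduce, and none relies on covariate adjustment. After the design effect, the analysed sample is worth 220 / 1.1 = 200 independent patients, so 100 per arm is the right basis for the next step.

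**2. Gain in precision.** Let r be the partial correlation of T0 BSI-53 with T2 APQ, given the covariates already listed. The document gives no r, so a range is assumed. Read d = 0.4 as standardized by the residual SD of the model as planned. Adding severity then gives:

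- residual variance × (1 − r²)
- standard error × √(1 − r²)
- standardized effect 0.4 / √(1 − r²)
- equivalent sample 200 / (1 − r²)

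| r | Residual variance | SE reduction | Power, 100 per arm | Equivalent patients |
|---|---|---|---|---|
| 0 | 1.00 | 0% | 80.4% | 200 |
| 0.1 | 0.99 | 0.5% | 80.8% | 202 |
| 0.2 | 0.96 | 2.0% | 81.9% | 208 |
| 0.3 | 0.91 | 4.6% | 83.9% | 220 |

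The gain is 0.4 to 3.5 percentage points. The power figures are for a single-outcome t-test. The actual primary test is a global test over five subscales, so they indicate size only.

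**3. Bias from selective loss.** This was a large-sample simulation. The outcome residual was Y = 0.4·A + r·S + √(1 − r²)·e, with A the arm, S severity in SD units, and r = −0.1, −0.2, −0.3 (more severe, worse parenting; Y scored so that higher is better). The log-odds of loss were −1.9 + g·S, giving 14–15% missing. Bias in the contrast with S left out:

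- Same dependence in both arms (g = 0.7 in each): within ±0.001 SD.
- MB-PC only (g = 0.7, and 0 in SCC+): 0.010, 0.021, 0.029 SD in favour of MB-PC.
- Opposite directions (g = 0.7 in MB-PC, −0.7 in SCC+): 0.022, 0.041, 0.056 SD. This is an extreme case.

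With S in the model the bias was at most 0.003 SD throughout. A variant with 52 therapy groups of 5, 15% loss, one-arm slopes of 0.7–1.2 and severity effects of 0.15–0.25 SD gave 0.015–0.036 SD. The realistic one-sided scenarios therefore span about 0.01 to 0.04 SD.

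For scale, the standard error of the contrast at 100 per arm is √(2/100) = 0.141 SD, so 0.015–0.036 SD is about 0.11–0.26 of a standard error. Under the null that would move a two-sided 5% error to about 5.1–5.7%.

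**The case against.** The strongest reply is that this is one more useful covariate and not an error. Much of that stands.

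- **A reader might infer that the plan contradicts its own rationale.** It does not. The guidance concerns which children face a higher risk of maltreatment. It does not say what predicts T2 APQ once five baseline APQ subscores are in the model. The remark about pathways does not mention severity. Adjusting for diagnosis in a sample with many disorders conflicts with neither statement.
- **A reader might infer that the result is biased or the trial underpowered.** With complete data, randomization keeps the contrast valid, and a chance imbalance in severity does not change that. The 260 patients were derived without credit for covariates.
- **A reader might infer that the model fails missing-at-random without severity.** That needs severity to predict both loss and T2 APQ beyond baseline APQ, setting, diagnosis and any T1 data, and for the contrast it needs the dependence to differ by arm. Stopping treatment is not the same as losing outcome data: section {18b} follows treatment drop-outs to T1 and T2, reimburses assessments and offers home visits at T2. The 15% is an upper figure.
- **The prognostic value is assumed.** Setting and diagnosis may already carry part of severity, so r could lie at the low end of the range.

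How diagnosis is grouped, and which variables enter the imputation planned in {20c}, are ordinary analysis-plan content and are not criticized here.

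What the reply does not remove is that the covariate list is spelled out, that it omits a plausible predictor already measured at T0, and that adding it serves the stated aim of adjustment. The multiple imputation in {20c} is a sensitivity analysis and does not sharpen the primary estimate.

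**Conclusion.** The point holds as a modest improvement. The primary analysis is valid as written and the sample size stands. Some precision is probably forgone: about 0.4 to 3.5 points of power at d = 0.4, equal to 2 to 20 extra patients on a base of 200, if the partial correlation lies between 0.1 and 0.3. That range is an assumption, and at its low end the gain is negligible. The protection against bias, about 0.01 to 0.04 SD or at most a tenth of the planned effect (0.04 / 0.4), matters only if severity-related loss of outcome data differs between arms. The document gives no evidence of this and takes steps against it. Priority: optional.

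**What to change.** In section {20a}, and correspondingly in the analysis plan, add the T0 BSI-53 global score as one continuous covariate to the primary model and to the analogous secondary models. Do this before any data analysis, because adding it after results are seen would look selective. Nothing else in the covariate list needs to change.

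The cost is one line of wording and one parameter per subscale. The value is already collected. The few patients with a missing T0 BSI-53 need a simple baseline imputation so that none drops out of the primary analysis.
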